Previous authors have studied through randomized controlled trials, the effectiveness of MI interventions in PD combined with gait exercises or regular physical therapy (14–17), dual-tasks (18–20), virtual reality (21, 22), and neurofeedback (23, 24). From those works that compare gait training or conventional physical practice with MI versus without MI, they report no differences post-training between groups in motor function after 24 sessions (17), 12 sessions (14), 6 sessions (16), and a single training session (15). Although these designs would allow it to analyze the proportion of improvements attributed to the MI technique, there are methodological considerations that may condition the previously mentioned results. The first of them, is the PD severity presented by the participants in the informed works, which ranges from mild to moderate. Although gait alterations can be observed from the initial stages of PD (8, 25, 26), these may be insufficient to show significant differences between groups post-training. Regarding to this, the non-instrumental measurement tools used (14, 16, 17) may be inadequate to detect small changes when participants do not present severe gait impairments. On the other hand, authors who include MI in gait physiotherapy and use biomechanics assessment tools, only report the effects of a single therapy session (15), therefore a minimum training dose is not given (27) that allows differences to be observed.

Another reason that may contribute to the fact that no differences are observed between therapy with and without MI is the non-stratified randomization of the participants (14–17), since decompensated groups could mask a possible superior effect of the gait physiotherapy supported by MI. Finally, and related to the sample size analyzed in the literature, these do not exceed 50 subjects (14–17), hence the sample size may underestimate the number of participants necessary to observe differences between groups if this is based on intragroup post-intervention change (14). Given the above, this study aims to determine the effect of adding MI exercises to gait training of people with mild-to-severe PD. We hypothesize that MI added to gait rehabilitation achieves a greater effect than isolated gait training in people with PD, and that this effect increases as the disease progresses, even when AO and walking exercise are exactly the same in control and experimental group.

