### Assignment of intervention and blinding

2.3

A stratified randomization process will be performed by the external research, considering the H&Y stages. Because patient recruitment will occur over a prolonged period, to control the stratification, the randomization will be performed after 12 participants group recruitment, and this process will be repeated six times, with the exception that the last group of recruitment will be of 14 people instead of 12. The allocation in each group of recruitment will be 1:1, using a function of Microsoft Excel (V18.0, 2021. Excel; Microsoft Corp). To ensure masking, the raters physiotherapist, and data analysis researcher, will be blinded to the participant’s allocation. Although participants and treating physiotherapists cannot be totally blinded to the intervention performed, the hypothesis and objectives of the study will be hidden from them. At the same time, all participants will be instructed not to disclose information regarding their intervention to the raters’ physiotherapists. To control expectancy effects, it will be explained to patients that it is not yet determined which therapy is more effective. On the other hand, a consecutive number code will be assigned to the participants without disclosing the treatment group to which they belong.

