A two-factor mixed Multivariate Analysis of Variance (MANOVA) will be conducted to analyze the factors effects on the outcomes registered at t0, t1, and t2. The within-subject factor is *Time* with three categories (Baseline, Postintervention and Follow-up). The between-subject factor is *Group* with two categories (GiG and GaG). When significant effects are found, Bonferroni will be used for post-hoc comparisons. Differences shall be declared statistically significant if *p* < 0.05. Before the referred statistical analysis above, the following assumptions will be checked: (1) Normality: the distributions of the residuals will be tested using the Shapiro–wilk test; (2) Sphericity: the homogeneity between variances of the differences between pairs of measures will be checked with the Mauchly sphericity test; (3) Homoscedasticity: homogeneity of variances will be evaluated using the Levene test; (4) Equality of covariance matrices: the equality of variance–covariance matrices across the cells formed by the between-subjects effects will be tested with the Box’s *M* test; (5) Absence of multicollinearity, the correlation level between dependent variables will be observed with the Pearson correlation test. If any of these assumptions are not met, the necessary statistical corrections will be used (61).

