Despite not reporting differences between groups, previous studies informed that gait physiotherapy with MI causes statistical changes in the total score of MiniBEST test, the Sensory orientation and Dynamic gait domain of balance assessment (14), the hip ROM, time of stance and swing phase of gait cycle (15), the mental section from UPDRS, and Schwab and England scale score for Activities of daily life (17). Furthermore, other authors have been informed of improvements in the Timed Up and Go test, the 10-meter walking test, and the score in the MiniBest balance test (20) when combining MI with dual-task; and MI combined with Neurofeedback has demonstrated improvement in endurance walking (23).

Even when we hypothesize that MI added to gait training could achieve a greater effect than detached gait training in people with PD, several factors or possible covariates must take into account to control the influence on the variance in dependent outcomes, such as the number of training sessions completed, average time elapsed between the medication doses intake and the start of the physiotherapy sessions, the stage of PD severity, and other between-groups factors like sex or level of activities in daily life, as the GAITimagery protocol contemplate. The methodological considerations that the GAITimagery trial has incorporated in the future development of this trial will allow us to analyze the effects of MI techniques in physiotherapy. The MI is an easily transferable to clinical practice technique because it does not require expensive materials or additional training for therapists, unlike other strategies such as neurofeedback or virtual reality. Nevertheless, it is necessary to study the ratio of gait improvement that can be explained by the MI aside from its superiority compared to not including MI in physiotherapy programs.

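### The hypothesis that the imagery effect grows with disease severity has no matching term in the Group-by-Time model, which also omits the H&Y stratification factor

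*Protocol article*

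**What the plan says.** The Introduction states a two-part hypothesis: imagery added to gait rehabilitation does better than gait training alone, "and that this effect increases as the disease progresses". Section 2.3 (Assignment of intervention and blinding) makes severity the stratification factor: "A stratified randomization process will be performed by the external research, considering the H&Y stages". Section 2.2.2 also pairs participants of equal H&Y stage within sessions, and Table 1 shows H&Y recorded at screening.

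Section 2.4 then fixes the analysis: "A two-factor mixed Multivariate Analysis of Variance (MANOVA) will be conducted to analyze the factors effects on the outcomes registered at t0, t1, and t2". Patients are classified between subjects by treatment arm alone, "with two categories (GiG and GaG", and the only other term is the repeated assessment of each patient, "with three categories (Baseline, Postintervention and Follow-up". Section 2.4 names no severity factor, covariate, interaction or subgroup analysis. Section 2.2.4 sizes the trial for two groups and three assessments, also without a severity term.

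The Discussion says that several factors or possible covariates have to be taken into account to control variance in the outcomes, including "the stage of PD severity, and other between-groups factors like sex or level of activities in daily life, as the GAITimagery protocol contemplate".

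**The concern.** A claim that the effect increases with severity is a claim of effect modification. Testing it needs a term that lets the Group effect differ by stage. The section 2.4 model counts its factors and lists their levels, and stage is not among them, so following it as written gives no estimate or test of the severity claim. Anyone wanting to address that claim later would have to choose the H&Y grouping, the outcome and the time point after seeing the data.

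The second issue is smaller. A factor that constrains the allocation is normally carried into the analysis so that the standard error reflects the design. Here the Discussion suggests that stage will be accounted for, while section 2.4 leaves it out, so the two sections do not agree.

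**Working it through.** **1. What the trial was sized for.** Inputs from section 2.2.4: f = 0.15, power 80%, alpha 5%, 2 groups, m = 3 times, N = 74. Assumed, because not stated: correlation between repeated measures rho = 0.5, sphericity holding. For the Group x Time interaction:

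- lambda = f² x N x m / (1 - rho) = 0.0225 x 74 x 3 / 0.5 = 9.99
- df1 = 2, df2 = (74 - 2) x 2 = 144
- power = 80.6% at N = 74 and 79.5% at N = 72

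The stated 74 is therefore reproduced as a Group x Time calculation with no severity term. The same test needs N = 102 at rho = 0.3 and 46 at rho = 0.7. A between-group main effect would need 236 at rho = 0.5.

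**2. What f = 0.15 means at t1.** If the groups differ by delta (in SD units) at t1 only, the interaction effects are ±delta/2 times (-1/3, 2/3, -1/3). Their mean square is (delta²/4) x (2/9) = delta²/18. So delta = 0.15 x √18 = 0.64 SD. An effect held equally at t1 and t2 gives the same value. Read instead as a plain two-group comparison, f = 0.15 is d = 2f = 0.3 SD. These are the two sizes tried below.

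**3. Power of a Group x H&Y interaction at t1.** Assume two severity strata of equal size. The SE of a two-group difference is 2/√N, and that of a difference between two half-sample effects is 4/√N = 4/√74 = 0.465 SD.

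| Difference in effect | z = d x √74 / 4 | Power |
|---|---|---|
| 0.64 SD | 1.37 | 28% |
| 0.3 SD | 0.65 | 10% |

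The 95% CI half-width is 1.96 x 0.465 = 0.91 SD. Adjusting for baseline gait speed multiplies the SE by √(1 - rho²). At rho = 0.5 that is 0.866, giving power of about 35% and 12%; at rho = 0.8 it is 0.6, giving about 63% and 19%.

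**4. Cross-check with the three-way term.** For Group x Severity x Time with two severity levels, a difference D between stratum effects corresponds to f = D/√72, so D = 0.64 gives f = 0.075. Power at N = 74 and rho = 0.5 is 27%, in line with step 3, and 80% would need N = 288. With three levels and f = 0.075, power is 20%. If the two-level interaction itself had f = 0.15, power would be 81%, but that is D = 0.15 x √72 = 1.27 SD, twice the planned effect.

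**5. Uneven strata.** Suppose the overall effect has 80% power and the difference between strata is as large as that effect. Interaction power is then 29% with an even split and 20% if one fifth of patients are in the severe stratum.

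**6. Leaving out a balanced stratum.** Let R² be the share of the analysed variance that the stratum explains (assumed; the documents give no value). The true SE is √(1 - R²) times the SE the model reports. Then actual alpha = 2 x [1 - Φ(1.96/√(1 - R²))], and power = Φ(2.80 - 1.96/√(1 - R²)) where the adjusted model has 80%.

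| R² | Actual alpha | Power |
|---|---|---|
| 0.1 | 0.039 | 77% |
| 0.2 | 0.028 | 73% |
| 0.3 | 0.019 | 68% |

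For Group x Time, R² refers to change over time. A severity effect on gait speed that is constant over time cancels from that test, so the relevant R² may be small.

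**The case against.** The strongest reply is that the severity claim is one subordinate clause. The stated aim in the Introduction concerns the effect of adding imagery, and the Discussion restates the hypothesis without severity. That limits the weight of the point, but the clause is still a stated hypothesis with no stated test.

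A second reply is that the Discussion does account for stage, and that its phrase about other between-groups factors could even be read as placing stage among the factors crossed with Group. The wording is ambiguous. The stated purpose there, however, is to control variance, and section 2.4 explicitly describes a two-factor model. A separate analysis plan may say more, but the point here is that the article's own sections do not agree.

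A reader might also infer more than the documents support:

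- *That the whole hypothesis is untested.* It is not; Group x Time tests superiority.
- *That stratification is wasted or ignored.* Balance between the groups, which is the reason the Introduction gives for stratifying, is kept whatever the model, and the Discussion does name stage.
- *That omitting H&Y inflates the variance by 1/(1 - R²), for instance 1.25 to 1.43 at R² of 0.2 to 0.3.* Those R² values are assumed and refer to an unadjusted t1 comparison, not the planned Group x Time test. Under stratified allocation the true variance is not raised; only the estimated SE is too large. The error is on the conservative side.

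**Conclusion.** The point holds in a limited form. The severity part of the hypothesis has no term in the section 2.4 model, and the stratification factor is missing from that model although the Discussion lists it as something to take into account. This rests on the text alone and needs no assumption.

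The cost to the main test is some possible loss of power, of a size the documents do not allow one to fix, with no excess of false positives. A severity interaction would be imprecise at N = 74. Power of about 28% and 10% assumes two equal strata and no baseline adjustment; uneven or more numerous strata lower it, and a strong baseline correlation raises it. The interaction is therefore worth estimating, but this trial is unlikely to settle it. The change should be made, but the main comparison remains valid without it.

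**What to change.** 1. In section 2.4, include the H&Y stratum used for randomisation in the gait-speed model together with its interaction with Time. A plain H&Y main effect would not sharpen Group x Time. For the t1 comparison, the equivalent is H&Y stratum as a covariate alongside baseline gait speed.
2. Prespecify one Group x H&Y interaction for gait speed at t1, with the H&Y grouping stated in advance. Report it as an estimate with 95% CI and label it secondary or exploratory because of its low power.
3. Align the Introduction, section 2.4 and the Discussion, and soften the severity claim to match what the trial can show.

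The cost is a revision of the analysis text and a few degrees of freedom, the exact number depending on how many strata are used, which the article does not state. No new data are needed, because H&Y is already recorded at screening.

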**Figure 4 fig4:**
[figure not shown]
Biomechanical model and anatomical placement of motion capture markers. **(A)** Dynamometric platform used in the biomechanical gait assessment. **(B)** Instrumentation of Inertial Sensor Units measure, which will be attached by elastic straps provided by the manufacturer. Each sensor must be placed at the following zones: **(B.1)** Lumbar, located just below the spinosa of the lumbar vertebra 5. **(B.2)** Thighs, located at the lower limit of the upper third of the thigh, on its lateral surface. It is considered as the total measurement of the thigh from the greater trochanter to the interarticular line. **(B.3)** Legs, placed at the midpoint of the leg measured from the interarticular line to the medial malleolus. The sensor is positioned just medial to the tibial border. **(B.4)** Feet, positioned on the dorsum of the foot, four centimeters from the intersection of the inter-malleolar line, above a line projected toward the fourth toe.

The study’s primary outcome is Gait speed at the post-training time (primary time point), defined as the distance traveled by the body per unit of time (m/s). The Gait speed is an objective variable, easy to measure with or without instrumental equipment, and considered a relevant indicator of functional and health status (54, 55). In addition, the secondary outcomes of this trial are the Maximum gait speed (m/s) (56) and the Gait speed variability, calculated through the coefficient of variation ([standard deviation/mean] × 100) (57), which indicates how stable or repeatable the participants are when walking. These variables could be more sensible to gait impairments (58) and changes after treatment (57). On the other hand, the tertiary outcomes are those from the spatiotemporal, kinematics, and kinetics gait analysis, in addition to the scores of the scales and questionnaires proposed in Table 1.

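### Preliminary significance tests decide whether the gait-speed analysis is altered, so the primary p value can depend on choices made after the data are seen

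*Protocol article*

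**What the plan says.** Section 2.2.3 makes gait speed at the post-training visit (t1) the primary outcome. Section 2.4 plans a mixed MANOVA with Group (two arms) and Time (three visits) as factors. It then puts a set of checks ahead of that analysis: "Before the referred statistical analysis above, the following assumptions will be checked". Four of the five are significance tests on the trial data:

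- normality: "the distributions of the residuals will be tested using the Shapiro–wilk test"
- sphericity: "the homogeneity between variances of the differences between pairs of measures will be checked with the Mauchly sphericity test"
- homoscedasticity: "homogeneity of variances will be evaluated using the Levene test"
- covariance matrices: "the equality of variance–covariance matrices across the cells formed by the between-subjects effects will be tested", by Box's M

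The fifth is a look at the correlations between outcomes. The consequence of a failure is given in one sentence, with one citation: "If any of these assumptions are not met, the necessary statistical corrections will be used". The text does not say which correction follows which failure, at what level the checks are tested, or whether the residuals are tested pooled, by visit, or by arm and visit.

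**The concern.** The rule makes the form of the primary analysis depend on preliminary tests of the same data, and a single rejection is enough to set it off. With several tests at 0.05, some rejections are expected when nothing is wrong. A correction would therefore be called for in a sizeable share of trials with perfectly behaved data.

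Two further features add to this. The corrections are open as written, so more than one p value for gait speed could qualify as the corrected one. One of the triggers is also misplaced: the multivariate tests of Time and of Group by Time do not assume sphericity, so a Mauchly rejection gives no reason to alter them. At stake is whether a reader of the results can tell that the reported method was the planned one, and whether the 5% level belongs to a procedure fixed in advance.

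**Working it through.** **The plan's own figure.** The article states no rate for the gate. Its only related figure is the sample size in section 2.2.4: 74 in total, from f = 0.15, 80% power, alpha 5%, 2 groups and 3 times. Take the univariate interaction F test with noncentrality λ = f²·N·m/(1−ρ), and assume ρ = 0.5 and ε = 1:

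λ = 0.0225 × 74 × 3 / 0.5 = 9.99 on 2 and 144 df, which gives power 0.806.

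So 74 is reproduced, and ρ = 0.5 is the correlation consistent with it.

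**Number of tests for gait speed alone.** There are three Levene tests (one per visit), one Mauchly test and one Box's M test. Shapiro-Wilk adds 1 (pooled residuals), 3 (by visit) or 6 (by arm and visit). The total is 6, 8 or 11. If the tests were independent and each at 0.05, the chance of at least one rejection would be:

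- 6 tests: 1 − 0.95⁶ = 26.5%
- 8 tests: 1 − 0.95⁸ = 33.7%
- 11 tests: 1 − 0.95¹¹ = 43.1%

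**Simulated rate with every assumption true.** The data were trivariate normal with compound symmetry and equal covariance matrices. There were 6,000 trials per setting (standard error about 0.6 points) and each test was at 0.05. The entries are the percentage of trials with at least one rejection.

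| Per arm | ρ | Pooled (6 tests) | By visit (8) | By arm and visit (11) |
|---|---|---|---|---|
| 37 | 0.5 | 26.2 | 32.2 | 41.7 |
| 37 | 0.7 | 32.0 | 31.4 | 40.7 |
| 37 | 0.8 | 35.8 | 30.9 | 39.8 |
| 37 | 0.9 | 44.8 | 27.0 | 35.1 |
| 44 | 0.5 | 26.5 | 31.0 | 40.8 |
| 44 | 0.7 | 30.3 | 30.7 | 39.4 |
| 44 | 0.8 | 35.8 | 29.6 | 38.7 |
| 44 | 0.9 | 43.7 | 26.0 | 35.4 |

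The range is about 26 to 45%. The pooled column rises with ρ because a participant's three residuals are correlated, and a pooled Shapiro-Wilk test ignores that. Testing Box's M at 0.001 lowers the by-visit and by-arm-and-visit columns by about 1 to 3 points.

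**Effect on the type I error of the interaction test.** These runs used the same kind of normal data, 37 or 44 per arm, ρ = 0.5 and 0.8, and 8,000 trials per setting (standard error about 0.24 points).

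- No gate, uncorrected test: 4.8 to 5.1%.
- Gate with one fixed rule (ranks if normality fails; otherwise Greenhouse-Geisser if Mauchly rejects; otherwise the multivariate test if Levene or Box's M rejects): 4.8 to 5.1%.
- Gate, then the smallest p of four analyses (uncorrected, Greenhouse-Geisser, multivariate, ranks): 5.5 to 6.2%.
- The same with a Mann-Whitney test of the t1 change added: 6.2 to 7.1%.

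Other runs used a different set of five (uncorrected or multivariate test, ranks of either, log). They gave 6.4% with normal data and 8.2% with mild skew (log-SD 0.3, an assumed value). With that skew the gate fired in about 95 to 98% of trials. A fixed rule of log transform plus Greenhouse-Geisser still held 4.8 to 5.2%.

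**The alternative.** In simulation, a comparison at t1 adjusted for baseline with HC3 standard errors had a type I error of 3.5 to 4.8%. Under a common assumed effect, its power was 66% against 59% for the interaction test at ρ = 0.5, and within about 1 point of it at ρ = 0.8. The reason can be seen directly. With n per arm, unit variance and a difference d at t1 that is either fully kept or fully lost at t2, the noncentralities are:

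- adjusted comparison: (n/2)·d²/(1−ρ²), on 1 df
- interaction: (n/2)·(2/3)d²/(1−ρ), on 2 df

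Their ratio is 1.5/(1+ρ). It is 1.00 at ρ = 0.5, where the saving of one degree of freedom is a clear gain, and 0.83 at ρ = 0.8, where that saving is roughly used up.

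**The case against.** The strongest reply is that the gate does no harm on its own. With one correction rule set in advance, the error rate stays near 5% even when the gate fires in almost every trial. Inflation needs an analyst who computes several analyses and reports the smallest p value, and nothing in the article permits that. This stands. A reader might infer that testing assumptions first inflates the type I error, or that the primary p value is in general settled after the data are seen. The documents support neither. With perfect data the planned analysis is left alone in roughly 55 to 74% of trials, and a correction fixed beforehand is still a fixed procedure.

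Second, the text speaks of corrections, not of replacing the analysis. A degrees-of-freedom adjustment after Mauchly leaves little choice. A statistical analysis plan that is not shown may say which correction follows which failure, and the article cites a source. This also stands, so the absence of that detail from an article is not the point here. What remains is the rule the article does state: significance tests decide whether the primary analysis is altered. A later mapping of failures to corrections would limit the freedom but keep that dependence.

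Third, the checks come before the efficacy analysis, and section 2.3 blinds the analyst to allocation. Keeping to that order would help. Blinding helps less, because a two-sided comparison of two coded arms gives the same p value whichever label is which.

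Fourth, sphericity does matter to a univariate interaction test, and the sample size is reproduced from one. This is fair. The Mauchly trigger is out of place only if the multivariate tests are used.

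**Conclusion.** The point holds in a limited form. The article ties the primary analysis to preliminary tests that, at an assumed 0.05 each, reject for gait speed in roughly 26 to 45% of trials with all assumptions true, and it leaves the resulting correction open. The primary p value can therefore depend on choices made after the data are seen.

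The possible cost is a type I error of about 5.5 to 8%, and only under free choice among corrections. Under a single fixed rule it is near 5%. The firing rate rests on three things the article does not give: the level of the checks, the layout of the normality tests, and the between-visit correlation (0.5 to 0.9 tried). The upper end of the error range also rests on an assumed mild skew. This is a change worth making because it is cheap. It is not evidence that the planned test is invalid.

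**What to change.** Name one primary analysis for gait speed at t1 and state that it is used whatever the diagnostics show. One suitable choice is a linear regression of t1 gait speed on arm and baseline gait speed, with heteroscedasticity-robust (HC3) standard errors. It addresses the stated primary time point and does not need sphericity, equal variances or equal covariance matrices.

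If a univariate repeated-measures test is kept, apply Greenhouse-Geisser always and drop the Mauchly pre-test. Use residual plots as diagnostics only, and label any transformed or rank-based analysis as a sensitivity analysis.

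The cost is analysis wording, with no change to visits, procedures or recruitment. The downside is a very small loss of efficiency if all assumptions hold and the between-visit correlation is high. HC3 was also slightly conservative in some of the simulated settings.
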